## **6.3 Statistical Analyses**

### **6.3.1 The general principle**

#### **Summary Statistics**

Summary tables (descriptive statistics and/or frequency tables) will be provided for all variables at different endpoints. For continuous variables, means and standard deviations will be presented, unless the variable has a skewed distribution, in which case medians, 25th and 75th percentiles will be presented. For categorical variables, the number and percentage of participants within each category will be presented. For each variable (continuous or categorical), the number of missing values will be reported.

#### **Statistical Comparisons Between Groups**

Continuous variables will be compared using a *t* test or Wilcoxon rank-sum test if data show serious deviations from a normal distribution. Categorical data or ordinal data will be compared using a Chi-square test or Fisher's exact test, as appropriate. All tests will be two-sided.

For the analysis of the primary and secondary outcomes, estimated treatment differences and associated 95% two-sided confidence intervals will be presented.

## **Multicenter study**

To estimate the overall variability of the center effects, we used the random center effects (RCE) accounting for center effects (1). Therefore, mixed-effect model was used for the primary outcome.

## **Missing data**

Efficacy analyses will be conducted in the intention-to treat (ITT) set, which will include all randomized subjects of whom the migraine days are measured in at least on post-baseline 1 cycle.

Missing data will be imputed by the last observation carried forward (LOCF) method (2). In addition, to examine sensitivity of the LOCF method imputed the missing data, we will perform a sensitivity analysis with multiple imputation method under the missing at random (MAR) assumption (3) for the primary outcome with missing data. Multiple imputations use the observed data to fill in the missing values repeatedly to give rise to multiple “pseudo-complete” datasets. We will impute the missing data 100 times using the following one of methods 1) regression imputation, if data sets with monotone missing patterns, or 2) Markov chain Monte Carlo imputation, if data sets with other patterns. For this we will use the SAS procedure Proc MI process. Each method will give rise to 100 different imputed data sets. We will fit our final model described before to each of these imputed datasets and then compute an overall estimate of the intervention effect as an average of the imputation specific estimates. The standard error of the overall intervention effect estimate will be calculated using Rubin’s formula. SAS procedure Proc MIANALYZE will be used to implement these tasks.

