#### **2.4.1.3 Sample Size**

According to the previous pilot study(23), we anticipated that the number of migraine days over 12 weeks would be 3.1(SD 2.7) days in the acupuncture group and 5.2 (SD 4.4) in the medication group. With a 2-sided significance level of 5% and power of 90%, 68 participants for each group would be required, as calculated by PASS 2008 software (NCSS, Kaysville, Utah, USA). With an estimated loss-to-follow-up rate of 20%, we planned to enroll a total of 172 participants with 86 participants per group.

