### **8.1 Statistical Analysis**

The primary study hypothesis is that acupuncture is different from medication in decreasing migraine days for women with MRM. The primary outcome is the change from baseline in average number of migraine days per perimenstrual period over cycles 1-3, assessed using headache diary data. The primary analysis will be intention-to-treat with the last observation carried forward (LOCF) method. Migraine days during perimenstrual period will be

summarized in each treatment group and compared using mixed-effect model.

The following secondary outcomes will be analyzed using the mixed-effect model, *t* test, Wilcoxon rank-sum test, Chi-square test or Fisher's exact test, as appropriate and the intent-to-treat principal:

1. Change from baseline in average number of migraine days per perimenstrual period over cycles 4-6
2. Change from baseline in average number of migraine days per outside perimenstrual period over cycles 1-3 and cycles 4-6
3. Change from baseline in mean migraine hours during perimenstrual period over cycles 1-3 and cycles 4-6
4. Change from baseline in mean migraine hours during outside perimenstrual period over cycles 1-3 and cycles 4-6
5. Change from baseline in mean pain VAS during perimenstrual period over cycles 1-3 and cycles 4-6
6. Change from baseline in mean pain VAS during outside perimenstrual period over cycles 1-3 and cycles 4-6
7. Proportion of participants with at least 50% reduction from baseline in number of migraine days during cycles 1-3 and cycles 4-6
8. Proportion of participants using acute pain medication during cycles 1-3 and cycles 4-6
9. Success rate of blinding at cycle 1.5 and cycle 3

A two-side test with  $p < 0.05$  will be considered significant for all analyses.

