### **Sensitivity Analyses for the Primary Outcome**

For the primary outcome, sensitivity analyses will be performed on the per-protocol (PP) set to assess the robustness of the study conclusion to the choice of analysis population. The PP set is a subset of the ITT, which includes all randomized participants who have no major protocol deviations.

In addition, sensitivity analyses will be performed using multiple imputation method for missing data to assess whether the primary outcome is robust to departure from imputed missing data using LOCF method.

There will be between and within-woman differences in menstrual cycle lengths which

inherently confound the outcomes. To evaluate this potential confounder, we will perform a sensitivity analysis that using menstrual cycle length as a control variable in a mixed-effect model.

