#### **6.3.4 Analyses for Secondary Outcome**

Efficacy analyses for all secondary outcomes will be performed in the ITT population observed cases, with imputation of missing data using LOCF method.

The mixed-effect model (using baseline value as a covariate, treatment as a fixed effect, and center as a random effect) will also be used for secondary outcomes of the changes from baseline in average number of migraine days per outside perimenstrual period, mean migraine hours during perimenstrual period and outside perimenstrual period, mean pain visual analogue scale (VAS) during perimenstrual period and outside perimenstrual period. For proportion of participants with at least 50% reduction from baseline in number of migraine days and proportion of participants using acute pain medication will be compared between groups using a Chi-square test or Fisher's exact test, as appropriate.

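### LOCF is the primary missing-data method and the only imputation for every secondary outcome; it puts on-treatment values into off-treatment cycles 4-6 unchecked, and can bias the cycles 1-3 average under some time courses and dropout patterns.

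*Supplement*

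**What the plan says.** Protocol 8.1: "The primary analysis will be intention-to-treat with the last observation carried forward (LOCF) method". SAP 6.3.1, under Missing data, repeats the rule: "Missing data will be imputed by the last observation carried forward (LOCF) method (2".

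SAP 6.3.4 extends it to the secondary outcomes: "Efficacy analyses for all secondary outcomes will be performed in the ITT population observed cases, with imputation of missing data using LOCF method". Those outcomes include every measure over cycles 4-6. Treatment is given in cycles 1-3 only, and cycles 4-6 are follow-up (schedule tables in both documents; protocol section 4).

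MI has a secondary role. SAP 6.3.1 says "we will perform a sensitivity analysis with multiple imputation method under the missing at random (MAR) assumption" and limits this to the primary outcome. It fixes 100 imputations, a regression or MCMC method according to the missingness pattern, and pooling by Rubin's formula. SAP 6.3.3 repeats that "sensitivity analyses will be performed using multiple imputation method for missing data".

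Protocol 2.4.1.3 sets the expected loss: "With an estimated loss-to-follow-up rate of 20%, we planned to enroll a total of 172 participants with 86 participants per group".

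The documents do not give the timing of losses, the expected effect in each cycle, or a reason for LOCF beyond a citation. They also do not say whether LOCF works on single cycles or on the phase average.

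**The concern.** LOCF assumes that a woman who leaves would have stayed at her last recorded value. Two features of this design put that in doubt.

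First, treatment stops after cycle 3. The cycles 4-6 outcomes are there to show whether benefit lasts without treatment. A woman lost by the end of cycle 3 has no off-treatment data, so LOCF gives her a treatment-phase value in all three follow-up cycles. If benefit fades, those outcomes partly measure the treated state.

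Second, the primary outcome averages three cycles. If outcomes change from cycle to cycle, freezing an early value distorts a woman's average. The distortion reaches the comparison when the arms' courses differ, or when outcomes change over cycles and dropout is unequal. Repeated acupuncture sessions and a perimenstrual drug could plausibly act at different speeds, but the documents say nothing on this.

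**Working it through.** **The plan's own figures.** Inputs from protocol 2.4.1.3: means 3.1 and 5.2, SDs 2.7 and 4.4, two-sided 5%, power 90%.
- Difference: 5.2 − 3.1 = 2.1. Root-mean-square SD: √((2.7² + 4.4²)/2) = 3.65.
- The normal formula gives 64 per group and the t test 65, against the stated 68. Power at 68 is 91.8% (normal) or 91.4% (Welch).
- Loss: 68/(1 − 0.20) = 85, against the stated 86.

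The planned size is adequate. What matters here is the 20%, about 17 of 86 women per arm.

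**Cycles 4-6.** Let p be the proportion of an arm lost by the end of cycle 3, and r the fraction of a 1-day on-treatment benefit that persists off treatment. Assume a flat benefit while on treatment.
- LOCF estimate of the arm's follow-up benefit: (1 − p)r + p.
- Overstatement: p(1 − r).

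| p | r = 0 | r = 0.5 | r = 0.8 | r = 1 |
|---|---|---|---|---|
| 0.20 | 0.20 | 0.10 | 0.04 | 0 |
| 0.10 | 0.10 | 0.05 | 0.02 | 0 |

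The 0.2 day is an upper bound: all 20% lost by the end of cycle 3 and the benefit gone entirely. If the 20% is spread evenly over six cycles, about 10% is lost by then and the second row applies. Women lost later carry an off-treatment value. The between-arm difference is biased by the difference between the two arms' overstatements, so it reaches 0.2 only if one arm's benefit fades and the other's does not.

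**Cycles 1-3, assumptions.** 86 per arm; between-woman and within-woman SD 0.9 day per cycle; adjustment for a three-cycle baseline mean; benefit 0.5/1.0/1.5 days on acupuncture and 1.0/1.0/1.0 on naproxen. Both average 1.0, so the true difference is 0. Dropout is random and split equally between after cycle 1 and after cycle 2.

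Acupuncture shortfall per woman lost:
- After cycle 1: 1.0 − 0.5 = 0.5.
- After cycle 2: 1.0 − (0.5 + 1.0 + 1.0)/3 = 0.167.
- Average: 0.333. On naproxen it is 0.

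Bias against acupuncture:
- 20% lost in each arm, all in this window: 0.2 × 0.333 = 0.067.
- 30% v 10%, all in this window: 0.3 × 0.333 = 0.10.
- 20% spread over six cycles, so about 6.7% in this window: 0.067 × 0.333 = 0.022.

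Standard error:
- Within-woman variance of the three-cycle mean is 0.81/3 = 0.27. It becomes 0.81 if frozen after cycle 1 and 0.81 × 5/9 = 0.45 if frozen after cycle 2.
- With 20% lost: 0.8 × 0.27 + 0.1 × 0.81 + 0.1 × 0.45 = 0.342.
- Residual variance after baseline adjustment: 0.81 + 0.342 − 0.81²/1.08 = 0.5445.
- SE = √(0.5445 × 2/86) = 0.1125. The 30% v 10% case has the same SE; the spread case has 0.1075.

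Rejection rate at nominal 5%, Φ(−1.96 + bias/SE) + Φ(−1.96 − bias/SE):

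| Dropout | Bias (day) | Bias/SE | Rejection |
|---|---|---|---|
| 20% v 20%, spread over six cycles | 0.022 | 0.21 | 5.5% |
| 20% v 20%, all after cycle 1 or 2 | 0.067 | 0.59 | 9.1% |
| 30% v 10%, all after cycle 1 or 2 | 0.100 | 0.89 | 14.4% |

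Simulation of the same model agrees, giving about 5-6%, 8-9% and 14%. Complete data give bias of at most 0.002 day.

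**When the bias vanishes.** With the same course in both arms and equal random dropout, the shortfalls cancel: bias 0, rejection about 5%. With the same building course (0.5/1.0/1.5) but 30% v 10% early loss, bias is (0.3 − 0.1) × 0.333 = 0.067, so unequal dropout alone is enough.

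**The case against.** **Timing of loss.** The larger error rates need every loss to fall after cycle 1 or 2. The 20% is a general allowance over a trial with three further follow-up cycles, and losses there do not touch the primary outcome. Women with no post-baseline cycle fall outside the set defined under Missing data and are not imputed. This stands, and is why a range is given.

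**The assumed null.** The 9% needs courses that cross and whose averages cancel exactly. This also stands. In that scenario the error runs against acupuncture. If a real effect builds up as 1/3, 2/3, 1 with equal dropout, LOCF shrinks it by 3.3% to 10% when all 20% is lost in cycles 1-3, and power with 86 per group falls from 96.5% to 92.4% at worst, still above 90%. The direction is not general: a simulation with a flat effect and outcome-dependent dropout gave −0.63 against a true −0.60.

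**MI is already planned.** For the primary outcome a material LOCF artefact should appear as a gap between the two analyses. This stands as mitigation, though LOCF would remain the headline if they differed. It does not reach the secondary outcomes.

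**Observed cases.** A reader might infer that SAP 6.3.4 contradicts itself by naming both observed cases and LOCF. The phrase can be read as women with at least one observed post-baseline cycle, with later gaps filled. It is loose wording to clarify, not a proven contradiction.

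**Conclusion.** The point holds and should be fixed. Its firmest part is cycles 4-6: LOCF carries treatment-phase values into off-treatment cycles, by up to 0.2 day per cycle in an arm for each 1-day benefit that fades completely, and no planned analysis would show it. This rests only on some women leaving by the end of cycle 3 and some benefit being lost off treatment.

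For the primary outcome the weakness is conditional. Under the assumed courses the bias is about 0.02 to 0.07 day with 20% loss in each arm, and 0.10 day with early loss of 30% v 10%. For scale, the planned difference is 2.1/3 = 0.7 day per cycle if 12 weeks is taken as three cycles, so these are about 3%, 10% and 14% of it.

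A reader might infer that the trial's type I error is not controlled, or that the primary result could not be trusted. The documents do not support that. They give no dropout timing and no per-cycle effects, the bias is nil in plausible cases, and the planned MI partly checks the primary result.

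**What to change.** Amend protocol 8.1 and SAP 6.3.1, 6.3.3 and 6.3.4.

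- **Primary analysis:** use the MI already specified, applied to per-cycle migraine days, with arm, centre, baseline and observed cycles in the imputation model. Alternatively, fit a repeated-measures mixed model to the per-cycle values with treatment by cycle, baseline and centre, and estimate the cycles 1-3 average contrast.
- **Cycles 4-6:** use the same approach. State that no treatment-phase value is carried into follow-up.
- **LOCF:** keep it as a sensitivity analysis, and state that it works cycle by cycle.
- **SAP 6.3.4:** replace the reference to observed cases with the name of the analysis set and the imputation rule.
- **Optional:** add a delta-adjusted MI, since no analysis allowing for data missing not at random is planned.

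The cost is wording, modest programming on top of MI code that is already planned, and slightly wider intervals.

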## **Multiple Comparisons**

Since only one primary outcome is defined, no adjustments to the significance level will be required to account for multiple testing.

For the analysis of the secondary and safety outcomes, no adjustment for multiple comparisons will be made.

## **Analysis Software**

For all statistical analyses, SAS 9.4 software will be used. All hypothesis testing will be carried out at the 5% (2-sided) significance level.

### **6.3.2 Demographics and Baseline Characteristics**

All data recorded at baseline will be summarized by group. Comparisons between groups will be done using the methodology described in section 6.3.1. Summaries will be presented for the ITT Set in both groups.

### **6.3.3 Analyses for Primary Outcome**

The cycle migraine days will be summarized by the mean and standard deviation (or median and interquartile range if data are skewed) in each group and compared using mixed-effect model adjusted for the baseline value, with treatment as a fixed effect, and center as a random effect. In case of serious violations of the model assumptions (normality and constant variance of the residuals), a log-transformation may be applied. If not appropriate, a Wilcoxon rank-sum test will be used. The effect of the treatment will be estimated by the difference (or ratio, in case of log-transformation) between treatments and will be presented along with its associated 95% confidence interval.

### **Sensitivity Analyses for the Primary Outcome**

For the primary outcome, sensitivity analyses will be performed on the per-protocol (PP) set to assess the robustness of the study conclusion to the choice of analysis population. The PP set is a subset of the ITT, which includes all randomized participants who have no major protocol deviations.

In addition, sensitivity analyses will be performed using multiple imputation method for missing data to assess whether the primary outcome is robust to departure from imputed missing data using LOCF method.

There will be between and within-woman differences in menstrual cycle lengths which

inherently confound the outcomes. To evaluate this potential confounder, we will perform a sensitivity analysis that using menstrual cycle length as a control variable in a mixed-effect model.

#### **6.3.4 Analyses for Secondary Outcome**

Efficacy analyses for all secondary outcomes will be performed in the ITT population observed cases, with imputation of missing data using LOCF method.

The mixed-effect model (using baseline value as a covariate, treatment as a fixed effect, and center as a random effect) will also be used for secondary outcomes of the changes from baseline in average number of migraine days per outside perimenstrual period, mean migraine hours during perimenstrual period and outside perimenstrual period, mean pain visual analogue scale (VAS) during perimenstrual period and outside perimenstrual period. For proportion of participants with at least 50% reduction from baseline in number of migraine days and proportion of participants using acute pain medication will be compared between groups using a Chi-square test or Fisher's exact test, as appropriate.

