#### **5.1.2 Secondary Efficacy outcomes**

1. Change from baseline in average number of migraine days per perimenstrual period over cycles 4-6
2. Change from baseline in average number of migraine days per outside perimenstrual period over cycles 1-3 and cycles 4-6
3. Change from baseline in mean migraine hours during perimenstrual period over cycles 1-3 and cycles 4-6
4. Change from baseline in mean migraine hours during outside perimenstrual period over cycles 1-3 and cycles 4-6
5. Change from baseline in mean pain visual analogue scale (VAS) during perimenstrual period over cycles 1-3 and cycles 4-6
6. Change from baseline in mean pain visual analogue scale (VAS) during outside perimenstrual period over cycles 1-3 and cycles 4-6
7. Proportion of participants with at least 50% reduction from baseline in number of migraine days during cycles 1-3 and cycles 4-6
8. Proportion of participants using acute pain medication during cycles 1-3 and cycles 4-6
9. Success rate of blinding at cycle 1.5 and cycle 3

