## **6.2 Study Populations**

All patients with randomization will be included in the analysis set regardless of whether they receive any treatment. According to the intention-to-treat principle, all analysis will be based on the randomization set. The intention-to-treat (ITT) set will include all randomized participants who have at least one treatment and one primary outcome measure. The per-protocol (PP) set will include all randomized participants who have no major protocol deviation. The safety set will include all randomized participants who receive at least one session of acupuncture.

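### SAP 6.3.4 names observed cases and LOCF in one sentence; LOCF is the likelier intention, but nothing stops it from carrying on-treatment values into the cycle 4–6 secondary outcomes

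*Supplement*

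**What the plan says.** SAP 6.3.4 gives the rule for every secondary efficacy outcome: "Efficacy analyses for all secondary outcomes will be performed in the ITT population observed cases, with imputation of missing data using LOCF method". The plan does not define observed cases and uses the term nowhere else.

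Four other places bear on it:
- SAP 6.3.1, Missing data, gives a general rule: "Missing data will be imputed by the last observation carried forward (LOCF) method". It is not limited to the primary outcome. The same section describes the efficacy set as "all randomized subjects of whom the migraine days are measured in at least on post-baseline 1 cycle", while SAP 6.2 defines the ITT set as "all randomized participants who have at least one treatment and one primary outcome measure".
- Protocol 8.1 says "The primary analysis will be intention-to-treat with the last observation carried forward (LOCF) method". For the secondary outcomes it lists tests and the intention-to-treat principle, with no imputation rule.
- SAP 6.3.3 adds a check for the primary outcome only: "sensitivity analyses will be performed using multiple imputation method for missing data to assess whether the primary outcome is robust". No such check is listed for a secondary outcome.
- Cycles 4–6 enter each of the first eight secondary outcomes in SAP 5.1.2. The first is "Change from baseline in average number of migraine days per perimenstrual period over cycles 4-6".

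The plan does not say whether LOCF may cross from the treatment phase (cycles 1–3) into follow-up (cycles 4–6).

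**The concern.** Observed-case analysis and LOCF give different data sets whenever a value is missing: one leaves the woman or cycle out, the other fills it in. For cycles 1–3 the difference is modest, because a carried value at least comes from the same phase. For cycles 4–6 it is not. A woman lost before cycle 4 is either absent or is scored in follow-up with a result recorded while she was being treated.

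The cycle 4–6 outcomes are the only post-treatment evidence in the trial. If the group difference fades after treatment stops, carried values hide part of the fading. With no second missing-data analysis planned for these outcomes, nothing in the planned output would show it.

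**Working it through.** **Inputs from the documents (protocol 2.4.1.3).** The plan enrols 172 women, 86 per group, "With an estimated loss-to-follow-up rate of 20"%. Planning means are 3.1 (SD 2.7) and 5.2 (SD 4.4) migraine days over 12 weeks.

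**The plan's own figures.** An exact t-test needs 65 per group. With the Wilcoxon efficiency factor, 65 × π/3 = 68.07, which matches the stated 68. Then 68/(1 − 0.20) = 85, against 86 planned. Only the 20% is used below. It implies 172 × 0.8 = 137.6, about 138 women with follow-up data, if all loss occurs before cycle 4.

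**Inputs that are assumed.**
- On-treatment difference 0.7 days per period: (5.2 − 3.1)/3. The planning figure is not stated to be perimenstrual.
- Per-cycle SD 1.3 and within-woman correlation 0.5.
- All loss before cycle 4 and unrelated to outcome; the carried value is one of cycles 1–3.
- Analysis by baseline-adjusted linear model.

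**Bias from carrying across phases.** Let d be the fraction lost, Δt the on-treatment difference and Δf the follow-up difference. Then LOCF estimates (1 − d)Δf + dΔt, so its bias is d(Δt − Δf).
- No lasting effect, d = 0.20: 0.20 × 0.7 = 0.14 days.
- Half the effect lasts, d = 0.20: 0.8 × 0.35 + 0.2 × 0.7 = 0.42, against a true 0.35.
- Full effect lasts: bias 0.

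**Rejection rate if no effect lasts.** With a standard error near 0.12, let x = bias/0.12. The rate is Φ(x − 1.96) + Φ(−x − 1.96).
- d = 0.20: x = 0.14/0.12 = 1.17, giving about 21%.
- d = 0.10: x = 0.07/0.12 = 0.58, giving about 9%.
- d = 0.05: x = 0.035/0.12 = 0.29, giving about 6%.

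Simulation (4,000 trials, 86 per group) agrees:

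| Loss before cycle 4 | Observed cases reject | LOCF rejects |
|---|---|---|
| 20% | about 5% | about 21% |
| 10% | about 6% | about 10% |
| 5% | about 5% | about 6% |

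Departures from 5% in the observed-case column are simulation error. At 20% loss the two verdicts differ in about 21% of trials if no effect lasts, and in about 14% if half lasts (power 82% against 94%). At 5% loss they differ in 4–5%. If the full effect lasts, both reject almost always.

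**A second model.** This one uses the planning SDs divided by 3, correlation 0.5 between phases, the treatment-phase mean carried forward and no baseline adjustment. At 20% loss:
- No difference left in follow-up: 5.4% (observed cases) against 12.5% (LOCF).
- Half the difference left: power 0.38 against 0.60; verdicts differ in 24% of trials.
- No change between phases: both estimate about 0.70 days; power 0.91 against 0.96; verdicts differ in 6%, through sample size alone.

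The direction is the same in both models. The size depends on the inputs.

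**The case against.** The strongest reply is that the plan does settle the matter. SAP 6.3.1 prescribes LOCF for missing data without limiting it to the primary outcome, whereas it does limit multiple imputation to that outcome. The second half of the 6.3.4 sentence repeats LOCF, and no observed-case analysis is described anywhere else. Observed cases can also be read loosely as ITT women with at least one measured post-baseline cycle, with LOCF for their gaps. Because SAP 6.2 and 6.3.1 define the ITT set differently, such a qualifier need not be idle.

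Much of this stands. A reader might infer that either data set could be reported with equal right as the planned one. The documents do not support that: an analyst who imputed nothing would go against both the general rule and the explicit LOCF clause.

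Two things remain. First, 6.3.4 is the specific rule and adds a qualifier that the general rule lacks, while protocol 8.1 gives LOCF only for the primary analysis, so the text is not clean. Second, settling on LOCF does not remove the cycle 4–6 problem but brings it about, because the carry-over between phases is unrestricted.

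It is also fair to say that the rejection rates measure LOCF bias under assumed fading and loss, not ambiguity as such. The 20% is an overall planning allowance with no timing. The assumed SD implies 1.3 × √(2/3) = 1.06 for a three-cycle mean, against 3.65/3 = 1.22 from the planning SDs. And the observed-case result is unbiased here only because loss was assumed unrelated to outcome.

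**Conclusion.** The point holds in a limited form. The wording of SAP 6.3.4 conflicts with itself. LOCF is the likelier intention, and the consequence to mend is unrestricted carry-over of on-treatment values into the cycle 4–6 outcomes, with no planned check to reveal it.

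The bias is the fraction lost times the amount by which the effect fades: up to 0.14 days per period at 20% loss if a 0.7-day difference disappears. In that case false rejection rises to between about 12% and 21%, depending on the model. At 5% loss the effect is negligible, and if the effect persists in full there is no bias.

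A reader might also infer that the two readings will give opposite significance in this trial. That is not shown; it depends on amounts of loss and fading that the documents do not give. Only secondary outcomes are concerned. The stated hypothesis makes no claim of durability, and the primary analysis has a clear LOCF rule with a multiple-imputation check.

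**What to change.** Before database lock and unblinding:
- Reword SAP 6.3.4 to name one main data set for the secondary outcomes, and make the missing-data rule in SAP 6.3.1 say the same. Delete the term observed cases or define it.
- State that values from cycles 1–3 are not carried into cycles 4–6. A woman with no observed cycle in follow-up then gets no value there. The others contribute the cycles observed in that phase, averaged over the number observed; the fixed divisor of 3 in protocol 2.4.4 would count a missing cycle as free of migraine.
- Analyse the continuous outcomes with the baseline-adjusted mixed model that 6.3.4 already plans. Its list omits perimenstrual migraine days over cycles 4–6, which should be added. Keep the planned tests for the two proportions.
- Report N per arm for each phase, and give the other version as a labelled sensitivity analysis.

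The cost is a short edit to two SAP sections, with no change to the sample size. The downside is that N for cycles 4–6 may fall to about 138, with slightly lower power.
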